2b) Personal dispositional innovativeness will mediate the relationship between staff demographics and attitudes toward EBI. Specifically, staff demographics (i.e., higher education level, shorter job tenure) will be associated with higher personal dispositional innovativeness, and personal dispositional innovativeness will be positively associated with attitudes toward EBI.

2c) Social networks indicating more connectivity and positive information regarding *Mujer Segura* will be positively associated with attitudes toward EBI.

2d) Attitudes toward EBI will meditate the relationship between personal dispositional innovativeness and implementation fidelity. Specifically, personal dispositional innovativeness will be positively associated with attitudes toward EBI, and attitudes toward EBI will be positively associated with implementation fidelity.

2e) More positive attitudes toward EBI will be associated with greater implementation fidelity.

2f) Greater fidelity will be associated with more positive FSW outcomes.

Aim 3: To determine whether the implementation of *Mujer Segura* by each CBO is associated with decreased sexual risk behaviors among Mexican FSWs over a six-month period (e.g., increased condom use with clients, reductions in STI incidence);

Hypothesis 3. As in the completed efficacy study, FSWs randomly assigned to the theory-based *Mujer Segura* intervention condition will show greater reductions in high risk sexual behavior with clients (i.e., fewer unprotected vaginal and anal sex acts, lower global STI incidence) at six-month follow-up as compared to FSWs who receive standard counseling.

Aim 4: To determine whether improvements in FSWs’ sexual risk behaviors are associated with variations in intervention fidelity and counselor competency.

Hypothesis 4. Among FSWs in the *Mujer Segura* condition, improvements in sexual behavior with clients at six-month follow-up (i.e., frequency of unprotected vaginal and anal sex, STI incidence) will be associated with higher levels of counselor competency and fidelity to the implementation model.

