***The Intervention: Level of the FSW***

A secondary aim of this study is to determine how FSW behavioral outcomes change concordant with the fidelity of the implementation of *Mujer Segura* at each CBO and with other organizational characteristics. FSW data will be gathered at baseline (prior to counseling) and again at six-month follow-up using measures employed in our previous work with Mexican FSWs (Project #051182), which was reviewed and approved by the IRB.

Baseline and Follow-up Interview. The baseline interview (~30 min) is theory-driven and has been administered to over 1,800 FSWs in Mexico-U.S. border cities. Per the recommendations of our Mexican collaborators, all measures will be administered by computer-assisted personal interviewing (CAPI). Reading ability is not a requirement of study participation. Using CAPI technology, the interviewer will read all questions and response categories to the participant and record the participant’s responses on a computerized form.In order to measure intervention effects, the interview will be repeated with each participant at a six-month follow-up appointment. The interview covers the following domains:

 Background Characteristics. These include socio-demographics, family background variables (e.g., number of children), and financial need (e.g., number of financial dependents).

 Contextual factors. Interview questions include working conditions: work setting (e.g., street), type of sex worker (e.g., brothel-based), nature of relationship with pimp or manager (if applicable) (e.g., control over client selection), client characteristics, demands for unprotected sex, amount received for protected vs. unprotected sex, and availability of condoms and sterile syringes.

 Substance Use. History, practices and environmental influences, including age at first use of alcohol and specific drugs, amount of alcohol consumed using the AUDIT; types of substances used alone and in combination, routes of administration, and injection practices.

 Mechanisms of Change. Consistent with our theoretical framework, we include measures of attitudes, intentions, and peer norms about safer injection and sex.

 HIV and STI Knowledge will be measured with an 18-item scale that assesses awareness of the importance of condom use with respect to HIV/STI prevention (alpha = 0.75 to 0.89).

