Aims 3 & 4: Due to potential non-independence of FSWs within CBOs, mixed linear models will be used to determine if participation in the *Mujer Segura* intervention was effective in improving sexual behavior outcomes (e.g., condom use, ratio of unprotected to protected sex) compared to the treatment-as-usual condition. Within this model, intervention condition, time, and the intervention-by-time interaction will be entered as our primary independent variables. Because participants will be nested within CBOs, this factor will be entered as a random effect. A first-order autoregressive process (a stationary AR[1] process) will be used to characterize the autocorrelation structure.

Our second set of analyses will examine efficacy of the intervention for reducing incident HIV and other STIs. We will compare intervention groups in terms of cumulative incidence and incidence density. In both cases, the numerator will be the number of women who acquire the STI in question during follow-up; for cumulative incidence, the denominator will be the total number of at-risk women, whereas for incidence density the denominator will be the total number of person years for at-risk women. For each HIV/STI outcome, Poisson regression will be used to determine if group differences are statistically significant. As an indication of effect size, we will calculate the Number Needed to Treat (NNT) for each STI outcome, where NNT represents the number of participants in the intervention who would need to be treated before one fewer person contracted the STI than would be the case had all participants received the comparison condition. Aim 4 will be addressed by using FSW behavioral outcomes described above (aim 3).

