***Intervention Study Participants (FSWs)***

The second set of participants in this research will be the FSWs who are recruited at each CBO to participate in the baseline and follow-up assessments and either the *Mujer Segura* counseling intervention or the “usual care” comparison condition. The recruitment goal for the study will be 960 female sex workers (FSWs) from the twelve anticipated sites (12 CBOs times 80 FSWs per site = 960). As with the staff participants (see above), we are uncertain whether the all of the currently projected sites will be able to meet this quota. We also face the uncertainty (particularly in the early phases of the study) whether, once the study has been started at a particular site, the staff will be able to carry it to completion due to factors beyond our or Mexfam’s control. Accordingly, we request flexibility in the per-clinic and overall figures for recruiting FSWs, up to a maximum of 1,090 for the entire study (in increase of 130, which is 13.5% more, or the equivalent of less than two additional sites).

We anticipate that participants will range in age from 18 to 50 years (mean approx. 33); mean level of educational attainment will be 6 years; 80% will be married or living in a common-law relationship; and 94% will have children.

Inclusion Criteria: To be eligible for this intervention, participants must be:

1) Biologically female,

2) At least 18 years old,

3) Report having exchanged sex for money, goods or drugs within the previous 30 days,

4) Report having unprotected vaginal or anal sex with a male client at least once during the previous month.

Exclusion Criteria:

1) Consistent use of condoms for vaginal and anal sex with all male clients during the previous month,

2) Known to be HIV+ or test HIV+ for the first time on-site at MexFam clinic,

3) Being under 18 years of age,

4) Being male or transgendered,

5) Being incapable of giving informed consent,

Because this study is designed to transport an established, efficacious intervention into a community-based setting, we must adhere to core elements of the established intervention, which was designed for women who are biologically female. In the original intervention design, transgendered persons were excluded because this subpopulation of FSWs would require different recruitment strategies and a targeted intervention to reflect unique sexual risk behaviors and sexual milieu.

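### Aim 3 names an unprotected-to-protected ratio that has no value for some eligible women; the count in Hypothesis 3, adjusted for baseline, is the better outcome

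*Protocol*

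**What the plan says.** The Aims 3 & 4 paragraph of the protocol (section 8, Data Analysis and Interpretation) assigns linear mixed models to "sexual behavior outcomes (e.g., condom use, ratio of unprotected to protected sex) compared to the treatment-as-usual condition". These are the only two behavioural outcomes that the paragraph names, and both are given as examples. On the fixed effects it says that "intervention condition, time, and the intervention-by-time interaction will be entered as our primary independent variables". CBO is a random effect, and no baseline covariate is named.

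Four other places bear on this:

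- **Visits.** Section 8 (The Intervention: Level of the FSW) has two: "FSW data will be gathered at baseline (prior to counseling) and again at six-month follow-up".
- **Eligibility.** Section 9 lists the criterion "Report having unprotected vaginal or anal sex with a male client at least once during the previous month". It sets no lower limit on protected acts.
- **Hypothesis 3.** Section 5 defines the expected reduction in risk as "i.e., fewer unprotected vaginal and anal sex acts, lower global STI incidence".
- **Power.** Section 8 bases the behavioural calculation on a 36% reduction in the mean number of unprotected acts, with 384 women per group and alpha .05. It tests the group-by-time interaction with controls unchanged, and states power above 78%.

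**The concern.** A ratio with protected acts in the denominator has no value when there are none. The eligibility rule admits such women at baseline, and nothing prevents the same at follow-up. The protocol gives no rule for this case.

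At six months the problem involves treatment. The intervention is meant to raise condom use, so it can change which women have a defined ratio. The contrast among women with a defined ratio is then conditioned on a consequence of treatment and loses the protection of randomisation. A mixed model still uses the baseline value of a woman whose follow-up ratio is undefined, but this does not repair the problem: her follow-up is missing because of its own value.

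The named outcome also differs from the one in the hypothesis and the power statement. Finally, the planned interaction does not use the baseline measurement to gain precision, although every woman is to provide one.

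**Working it through.** **1. Where the ratio fails.** Let U be unprotected acts and P protected acts. Eligibility gives U ≥ 1 in the screening month and P ≥ 0. At P = 0, U/P does not exist. At follow-up a woman with no client sex gives 0/0, also undefined.

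**2. How it behaves near the boundary.** Take a woman with 20 acts:

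| U | P | U/P | U/(U+P) |
|---|---|---|---|
| 20 | 0 | undefined | 1.00 |
| 19 | 1 | 19 | 0.95 |
| 10 | 10 | 1 | 0.50 |
| 5 | 15 | 0.33 | 0.25 |

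Going from 19 to 10 unprotected acts moves the ratio by 18. Going from 10 to 5 moves it by 0.67. A linear model of the mean is therefore driven by women with one or two protected acts. The first two rows also show the selection at work: a woman who improves from 20 unprotected acts to 19 goes from having no value to having one of the largest, and so raises her arm's mean ratio. The count (20 to 19) and the proportion (1.00 to 0.95) both move in the right direction.

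**3. The protocol's own figures.** The group size reproduces: 960 × (1 − 0.20) / 2 = 384. The 78% power can be neither confirmed nor refuted, because no mean or SD is given. Back-solving with a two-sided test (sidedness is not stated for Aim 3) gives a standardised difference of (1.960 + 0.772) × √(2/384) = 0.197.

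**4. Change against baseline adjustment.** With two visits and complete pairs, the group-by-time term is the difference between arms in mean change. Take equal variance σ² at both visits, within-woman correlation ρ and comparable baselines:

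- variance of change: 2σ²(1 − ρ)
- variance of follow-up adjusted for baseline: σ²(1 − ρ²)
- ratio of the second to the first: (1 + ρ)/2, which is below 1 for every ρ < 1

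The protocol gives no ρ, so a range is shown. If the .78 refers to the change contrast, adjusted power is Φ(2.732/√ratio − 1.960):

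| ρ | Variance ratio | Adjusted power at 384 per group | n per group for .78 |
|---|---|---|---|
| .2 | .60 | .94 | 231 |
| .5 | .75 | .88 | 288 |
| .7 | .85 | .84 | 327 |

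If the 0.197 is instead on the SD of a single visit, power for change against adjusted follow-up is .58 against .80 (ρ = .2), .78 against .88 (ρ = .5) and .94 against .97 (ρ = .7). The direction is the same; the size depends on ρ and on how the .78 was computed. These figures are for a linear model and only indicate what a log-link model would gain.

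**5. When baseline is taken.** Section 8, Phase One, has women randomised to the experimental condition come back later for both assessment and counselling. Their baseline therefore follows randomisation and is taken later than the control arm's. The variance ratio above assumes that this does not shift the baseline. A later interview also covers a later period than the screening question, so a baseline count of zero is possible, and a plain log of the baseline count would fail.

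**The case against.** The strongest reply is that little rests on the ratio. It is one example; Hypothesis 3 and the power statement use counts, and a rule for zero denominators could sit in an SAP that is not shown. The interaction tested is the one that was powered, group-by-time is an accepted analysis, and calling these terms primary does not bar covariates. Much of this stands, and it limits the point to the choice of named outcome and the unused precision. It does not rescue the ratio: no coding rule gives a natural value at P = 0, and any rule chosen would determine the largest values in the data.

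Some stronger readings are tempting but not supported:

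- **That Aim 3 as a whole rests on the ratio.** The examples and the wording of Hypothesis 3 contradict this.
- **That the plan deletes its highest-risk women.** No section excludes anyone on this ground. Nor are the undefined women all high risk: one unprotected and no protected act is a low count, and no client sex at follow-up is low risk.
- **That a known share of women is affected.** The documents give no distribution of acts, so any share would reflect the distribution assumed.
- **That the covariance structure spoils the test.** The protocol says that "A first-order autoregressive process (a stationary AR[1] process) will be used to characterize the autocorrelation structure", which imposes equal variance at both visits. With complete pairs, the equal-variance fit estimates the variance of change as 2 × (S11 + S22)/2 − 2 × S12 = S11 + S22 − 2 × S12 (S11 and S22 the variances at the two visits, S12 their covariance). An unstructured matrix gives the same value.

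**Conclusion.** The point holds for the outcome and, with conditions, for precision. The ratio is undefined for some women whom the protocol admits, unstable when protected acts are few, and open at follow-up to selection by the behaviour under treatment. It also differs from the outcome that was hypothesised and powered. That much follows from the definition and the eligibility rule, without any assumed distribution.

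The precision loss is certain in direction under equal variances, complete pairs and comparable baselines: 40%, 25% and 15% of the variance at ρ = .2, .5 and .7. The margin is useful because the power statement assumes unchanged controls, while section 16 reports that controls in the parent study also reduced unprotected sex. The gain is not guaranteed, since the experimental arm's baseline is delayed until after randomisation. The planned change analysis is valid but less efficient; it is not an error.

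**What to change.** - **Outcome.** Replace the ratio with the six-month count of unprotected vaginal and anal acts with clients. Analyse it in a log-link count model (negative binomial, or Poisson with robust variance) with condition and CBO in the model, and report the rate ratio. This also fits an effect stated as a percentage reduction in a mean.
- **Relative measure, if wanted.** Use unprotected/(unprotected + protected). State the rule for women with no acts and report their number by arm.
- **Baseline.** Adjust for the baseline count in a form defined at zero, such as log(count + 1).
- **Delayed baseline.** Compare baseline values between arms and report the two-visit change analysis as a sensitivity analysis. If baselines differ, the two analyses can disagree and both should be shown.

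The cost is analysis wording: no new visits, participants or measurements. The downside is that the effect is a rate ratio rather than a mean difference, so mean counts by arm should be given beside it. The change should be fixed before outcome data are examined, so that handling of zero denominators is not chosen after seeing the results.

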***Data Analysis and Interpretation***

Aim 1: Equivalence testing will be used to evaluate Aim 1 using Schuirmann’s (1987) test of equivalence. A nominal alpha of .05 will be used in the proposed analysis. Given the nested data structure (i.e., service providers nested in CBOs), hierarchical linear modeling will be used to adjust standard errors for possible dependency among observations. The outcome of interest in Aim 1 focuses on *Mujer Segura* fidelity. We expect that service providers will attain approximately 90% treatment fidelity when considering that 100% is perfect fidelity.

Power calculations for equivalence tests proposed for Aim 1 were conducted using SAS® Proc Power. Using the bounds and nominal alpha specified above, along with a hypothesized difference between population group means of zero and a standard deviation of 15 in each group, the proposed sample size of 120 (10 staff x 12 CBOs) would yield power of >.89 to reject the null hypothesis of mean differences in favor of the alternative of group equivalence. This power calculation is based on the assumption that observations are independent. If the observations are dependent, this will be an overestimate of statistical power. One method of calculating power in this case is to estimate the degree to which the variance will be increased due to non-independence. Specifically, the variance will be increased by a factor of 1+(m-1)*ICC, also known as the design effect, where m is the average cluster size and ICC is the intraclass correlation coefficient. While we don’t have prior ICCs for *Mujer Segura* fidelity ratings, in our work examining service provider attitudes toward EBI implementation in CBOs, ICCs were generally low. However, in a larger and more representative study of CBOs across the U.S., the ICC was .03, and we expect the fidelity ICC to be of similar magnitude. Using the average ICC of .03 from this recent study, and an average cluster size of 8, the variance is estimated to be increased by a factor of 1.21. Given a total sample size of 96, the functional sample size would be 79.34 (i.e., total sample size/design effect), which would yield power of .80.

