Aim 2: Analyses will be informed by the conceptual model proposed by [name] and adapted for this study in which implementation of EBI results in effects of organizational and provider characteristics on provider attitudes, fidelity and outcomes. Conversely, introduction of an EBI can impact organizational and—to a lesser extent—provider characteristics. In particular, we will examine changes in organizational processes (i.e., culture, climate) and group process characteristics (e.g., organizational support) as a function of *Mujer Segura* implementation. We will also examine the relationship between individual organizational factors and provider characteristics, and their impact on the implementation of *Mujer Segura*. We will then examine whether more knowledge and higher levels of perceived utility are associated with better fidelity and outcomes. In all CBOs, we will examine the degree to which Leadership and Organizational Support are associated with more positive Attitudes Toward Evidence-Based Practice, fidelity, and outcomes. We will also examine the degree to which Personal Dispositional Innovativeness and other provider characteristics such as age, education level, experience, and job tenure are associated with Attitudes Toward Evidence-Based Interventions, fidelity, and outcomes. Quantitative hypotheses to be examined include:

2a) More positive organizational culture and climate will be associated with more positive attitudes toward EBI.

2b) Personal dispositional innovativeness will mediate the relationship between staff demographics and attitudes toward EBI. Specifically, staff demographics (i.e., higher education level, shorter job tenure) will be associated with higher personal dispositional innovativeness, and personal dispositional innovativeness will be positively associated with attitudes toward EBI.

2c) Social networks indicating more connectivity and positive information regarding *Mujer Segura* will be positively associated with attitudes toward EBI.

2d) Attitudes toward EBI will meditate the relationship between personal dispositional innovativeness and implementation fidelity. Specifically, personal dispositional innovativeness will be positively associated with attitudes toward EBI, and attitudes toward EBI will be positively associated with implementation fidelity.

2e) More positive attitudes toward EBI will be associated with greater implementation fidelity.

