We evaluated statistical power to detect main effects and interaction effects in Hypotheses 3 and 4. Our power analyses reveal that we have an excellent chance of detecting significant main effects and interactions in our data. Hypothesis 3 uses a repeated measures design with two conditions. Assuming an attrition rate of 20%, which we achieved in *Mujer Segura*, we will have 384 subjects per group for a total of 768 subjects at the end of five years. We used findings from the parent project intervention with FSWs described in Preliminary Studies to estimate overall reductions in high-risk sex and incident STIs. We observed a 36% reduction in unprotected sex in the intervention (i.e., 18% vs. 36%), and a 40% decrease in overall STI incidence in the intervention group relative to the control (i.e., 20% vs. 38%). To estimate power in our sample, assuming a 36% reduction in unprotected sex at six-month follow-up, we calculated the following: N=384 per group, alpha = .05, and a 36% reduction in mean number of unprotected sex acts. If subjects in our experimental condition reduced the number of unprotected sex acts while the control condition did not change (i.e., group x time interaction), we would detect significant differences greater than 78% of the time. Power is slightly higher for STIs (i.e., .81). The addition of a covariate for fidelity to test hypothesis 4 does not substantially impact power estimates. Therefore, though our study is not designed to replicate findings from the parent project, we have sufficient power to detect differences between groups.

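### Hypothesis 4 tests a largely counselor-level fidelity score with no counselor term in the model, so its standard error is modestly too small

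*Protocol*

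**What the plan says.** Section 8, Data Analysis and Interpretation, treats Aims 3 and 4 under one heading. In the mixed linear model, "intervention condition, time, and the intervention-by-time interaction will be entered as our primary independent variables". The clustering provision is "Because participants will be nested within CBOs, this factor will be entered as a random effect", with a first-order autoregressive structure for the repeated measurements. No other grouping factor is named.

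Aim 4 gets one sentence, which points back to the Aim 3 behavioral outcomes. The power paragraph shows how fidelity enters: "The addition of a covariate for fidelity to test hypothesis 4 does not substantially impact power estimates".

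Hypothesis 4 (Section 5) is limited to women in the Mujer Segura arm. It says that their improvements at six months "will be associated with higher levels of counselor competency and fidelity to the implementation model".

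Under Aim 1 the provider level is recognised: "Given the nested data structure (i.e., service providers nested in CBOs), hierarchical linear modeling will be used". Under Aim 2 the conceptual model expects "effects of organizational and provider characteristics on provider attitudes, fidelity and outcomes".

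**The concern.** The predictor in Hypothesis 4 belongs mainly to the counselor. Women seen by the same counselor share much of its value, and their outcomes may be alike for other reasons tied to her. A CBO random effect accounts for likeness among women of one clinic, but not for the extra likeness among women of one counselor. The fidelity slope is then judged against woman-level error, although the predictor varies over at most 12 × 8 = 96 counselors.

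The Protocol applies provider-level thinking elsewhere. Hypothesis 2f, a closely related association, is powered on 96 providers, or 79.34 after allowance for clustering. Hypothesis 4 is treated as a covariate that barely alters power computed on 384 women per group.

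At stake is whether a reported link between counselor fidelity and women's outcomes has the error rate claimed for it, in a study meant to guide national scale-up.

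**Working it through.** **Inputs from the Protocol.** Twelve CBOs; eight counselors per CBO (Section 7, selection of CBOs); 40 intervention women per CBO (Section 8, Phase One); 20% attrition and alpha .05 (power text for Aims 3 and 4); ICC .03 for providers within CBOs (Aim 1). No ICC is given for women within counselor. Two-sided testing is stated only for Aim 2 and is assumed here.

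**The Protocol's own figures.**
- Design effect: 1 + (8 − 1) × .03 = 1.21. Functional sample size: 96 / 1.21 = 79.34. Both agree.
- Power for r = .30, as Φ(atanh(.30) × √(N − 3) − 1.96): .847 at N = 96 (stated .85) and .772 at N = 79.34 (stated .78). Both agree to within the approximation.
- Retained women per arm: 960 × .8 / 2 = 384. Agrees.

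No error rate or separate power figure is given for the Hypothesis 4 slope.

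**Women per counselor.** 40 × .8 = 32 retained per CBO; 32 / 8 = 4 per counselor (5 before attrition).

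**True level when counselor clustering is ignored.** For a covariate shared by all m women of a counselor, the variance of the slope is understated by D = 1 + (m − 1) × ICC. The true two-sided level is 2 × [1 − Φ(1.96 / √D)].

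| Counselor ICC | D, m = 4 | True level, m = 4 | True level, m = 5 |
|---|---|---|---|
| .03 (borrowed from Aim 1) | 1.09 | .061 | .064 |
| .05 (assumed) | 1.15 | .068 | .074 |
| .10 (assumed) | 1.30 | .086 | .098 |

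**Simulation.** The setting was 12 CBOs × 8 counselors × 4 women, no true fidelity effect, no CBO-level common cause, CBO outcome ICC .03, and 6,000 replicates. A model with only a CBO random intercept rejected at .051, .064, .069 and .089 for counselor ICC 0, .03, .05 and .10. Taking the counselor as the error unit, with fidelity centred within CBO, gave .049 to .052 in the same settings.

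**If the test is on change.** Hypothesis 4 speaks of improvements, so fidelity by time is a natural reading. A CBO intercept that is constant over time cancels from a change score. Ordinary regression of change rejected at .057 with no counselor variance, and at .073, .076 and .097 for counselor ICC .03, .05 and .10. A counselor intercept that is constant over time would cancel in the same way, so the counselor effect must sit on the scale tested.

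**If fidelity is not fully shared.** Section 5 says fidelity is measured partly from the women's own reports. If a share s of its variance lies between counselors, D is approximately 1 + (m − 1) × s × ICC. With s = .5 (assumed) and m = 4, ICC .03 gives D = 1.045 and a level of about .055; ICC .10 gives D = 1.15 and .068.

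**The case against.** **The Hypothesis 4 model is not written out.** The Aim 3 model contains condition, which cannot vary in a hypothesis confined to one arm, and an analysis plan that is not shown could add a counselor level. This stands as a limit. Still, the shared heading, the cross-reference to Aim 3 and the covariate sentence support only one model, and it has CBO as its sole named random factor.

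**The size is small.** At the Protocol's own .03 the level is about .06, and less if scores are specific to a session or a woman. This stands, and the point is sized accordingly.

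**Other analyses cover related ground.** Hypothesis 2f relates fidelity to women's outcomes with hierarchical modeling and providers as the sample. That lessens dependence on one slope but does not correct the Hypothesis 4 test.

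**A stronger reading is tempting.** Because the Protocol will examine "the degree to which Leadership and Organizational Support are associated with more positive Attitudes Toward Evidence-Based Practice, fidelity, and outcomes", a reader might infer that the slope is confounded by CBO quality, that detecting it would be a false positive, and that Hypothesis 4 must be read only from within-CBO deviations. The documents do not support this. Section 8, under the heading on the level of the FSW, asks how outcomes move with fidelity at each CBO, and Hypothesis 4 is worded as an association. Between-CBO association is therefore part of the question, and removing it would change the estimand. The larger rates obtainable by adding CBO confounding (up to .258 in an extreme simulated case) depend on a CBO share of fidelity variance and a correlation that the Protocol does not give. What remains is a caution about interpretation.

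**Conclusion.** The point holds, and its size is modest. As written, the Hypothesis 4 slope is tested without the counselor level, so its standard error is too small. The true level is about .06 at a counselor ICC of .03 and about .07 to .09 at .05 to .10. The .03 is borrowed from providers within CBOs, and the larger values are assumptions. The figures also assume about four retained women per counselor and a score that is mostly common to a counselor's women; they shrink to the extent that it is not.

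Separately, since the Protocol expects organizational characteristics to act on both fidelity and outcomes, the pooled slope combines differences between counselors with differences between CBOs. It is a legitimate answer to the association in Hypothesis 4, but not evidence of a pure counselor effect.

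**What to change.** For Hypothesis 4, state the model and add a counselor random effect nested within CBO. If the test is on change or fidelity by time, place that effect on the change or time term. Keep each woman's counselor identifier in the analysis file.

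State that the pooled fidelity slope is not to be read as a counselor effect alone. As a supporting analysis, enter fidelity as the CBO mean plus the counselor's deviation and report both terms, noting that the CBO-mean term rests on 12 units. This should not replace the Hypothesis 4 estimand.

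The cost is wording and one identifier, with no added participants or visits. The confidence interval for the slope widens by about √1.09 = 1.04 at ICC .03 and √1.30 = 1.14 at ICC .10.
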